**Discussion:**

Recurrent or persistent pain is common in the German population and causes high costs for patients and society. The A-IMPT aims to improve pain and pain-related impairments in pain patients at risk of chronification, thereby reducing the risk of developing chronic pain with its high socioeconomic burden. This new therapy could easily be integrated into existing therapy programs if positively evaluated.

Trial registration

The trial PAIN2.0 has been registered in the German Clinical Trials Register (DRKS) since 21/11/2022 with the ID DRKS00030773 [https://drks.de/search/de/trial/DRKS00030773].

This publication provides an update to the original study protocol, which was first published on 23 February 2024 [https://doi.org/10.1186/s13063-024-07975-4, BMC Trials]. Due to recruitment problems during the course of the project, the originally planned number of cases could not be achieved. In order to be able to provide sufficient information about the primary effects of the study, the number of primary endpoints was reduced from 3 to 2. The primary analysis period is now 6 months without including an additional measurement point after 3 months.

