### Outcomes {12}

#### Primary outcomes

The primary outcomes are (1) characteristic pain intensity (PI) and (2) disability score (DS) for pain-related impairment. PI and DS are collected at baseline (*t*_0_) and at 3-, 6-, 9- and 12-month follow-up (*t*_1_ to *t*_4_). Changes in the primary outcomes between baseline (*t*_0_) and 6-month follow-up (*t*_2_) are evaluated as primary endpoints. Data are collected through a patient questionnaire, which includes the following:

(1) Characteristic pain intensity and (2) disability score are components of the Von Korff Chronic Pain Grade Scale (CPGS) [16]. The CPGS is a multidimensional measure with 7 items covering the two mentioned dimensions of overall chronic pain severity. The PI score is calculated as the average of three 0–10 ratings for ‘pain right now’, ‘average pain’ and ‘worst pain’, which is then multiplied by 10 to obtain a 0–100 score. The DS score is derived from the average of three 0–10 ratings for ‘daily activities’, ‘social activities’, and ‘work activities’, also multiplied by 10 to produce a 0–100 score. The last item covers the disability days.

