**Additional variables**							
***Control***	Therapy expectation	X					
***Process***	Physical activity	X	X	X	X		X
	Flexible self-regulation	X	X	X	X		X
	Health literacy	X	X	X	X		X

^1^Additional follow-up for control and process variables, 5th week of intervention

^2^Data is available 6–9 month after treatment delivery

During the course of the project, the number of primary outcomes was reduced from three to two. PI and DS are the primary outcomes, while satisfaction with intervention, previously also a primary outcome, is now considered a secondary outcome. This change was necessary to ensure that the main effects of the intervention could be analysed with sufficient power, given the number of cases available.

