### Statistical methods

#### Statistical methods for primary and secondary outcomes {20a}

The primary analysis model for the two primary outcomes (pain intensity and disability score at 6 months adjusted for baseline values) is a linear mixed regression model with a random intercept.

The values of the primary outcomes at time *t*_3_ (6-month follow-up) serve as the dependent variables. To describe the effect of the intervention, the baseline value at time t_0_ and group membership are used as predictor variables [38, 39]. As two primary endpoints are analysed simultaneously, adjustment for multiple testing using Bonferron’s method will be applied.

When using these models, it is possible to include further predictor variables in the analysis. This can be of interest if, despite randomisation, relevant differences occur between the study arms and must be statistically controlled, or if the effects of covariates (e.g. of age or other patient characteristics) are to be analysed. Through appropriate model specification, all hypotheses of interest can be tested with these analysis methods.

The analysis of the primary endpoints will be conducted according to the intention to treat (ITT) principle.

The primary and secondary outcomes to be investigated are predominantly continuous data for which linear regression models can be used. However, the family of (generalised) mixed models also allows analogous evaluations for other types (ordinal or categorical) of dependent variables.

In the context of the analysis of days of incapacity to work or cost data, it may furthermore be necessary to use special analysis methods for data with an asymmetric distribution or with heavily populated zero cells (‘zero-inflated’).

Statistical significance tests are performed with an α-level of 0.05 (two-sided). In the confirmatory analysis of the primary outcome measures, a Bonferroni adjustment for multiple testing (3 outcome measures, 2 follow-up times) is applied. No such adjustment is used in the exploratory analyses of the secondary outcomes.

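### The confirmatory Bonferroni adjustment is still counted over 3 outcomes and 2 follow-up times, although the trial now has 2 primary outcomes at 1 time point

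*Protocol article*

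**What the plan says.** All sources are in the protocol article.

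- **Section {20a}, second paragraph:** "As two primary endpoints are analysed simultaneously, adjustment for multiple testing using Bonferron’s method will be applied". The model described there is for pain intensity (PI) and disability score (DS) at 6 months, adjusted for baseline.
- **Section {20a}, last paragraph:** tests are two-sided at 0.05, and for the confirmatory analysis of the primary outcomes "a Bonferroni adjustment for multiple testing (3 outcome measures, 2 follow-up times) is applied".
- **Abstract, update note under trial registration:** "the number of primary endpoints was reduced from 3 to 2", and "The primary analysis period is now 6 months without including an additional measurement point after 3 months".
- **Section {12}, Primary outcomes:** changes in PI and DS from t0 to t2 "are evaluated as primary endpoints".
- **Text below Table 2:** "the number of primary outcomes was reduced from three to two", with satisfaction moved to the secondary outcomes. The stated reason is to keep enough power with the cases available. The Trial status section repeats the change.
- **Section {14}, Sample size:** recalculated for two primary endpoints at the 6-month time point, with a difference of 0.3, residual variance 1.0, 80% power and two-sided 0.05, giving 500 cases for analysis.

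**The concern.** Both sentences in section {20a} govern the same two tests, PI and DS at 6 months, and they cannot both apply. Neither number in the closing bracket describes the current trial: there are two primary outcomes, not three, and one primary follow-up time, not two.

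This adjustment sets the threshold for the trial's only confirmatory claims. If it is unclear, the success criterion can be settled after the results are known. In an unblinded trial with patient-reported outcomes that would be hard to defend, even with an honest choice. Read literally, the closing sentence also gives away power that the reduction in primary endpoints was meant to secure.

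**Working it through.** **1. Implied thresholds.** The plan prints no adjusted alpha, so both values follow from the stated test counts and the overall two-sided 0.05.

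| Rule | Tests counted | Alpha per test | Critical absolute z |
|---|---|---|---|
| Second paragraph | 2 outcomes × 1 time = 2 | 0.05/2 = 0.025 | 2.241 |
| Last paragraph | 3 outcomes × 2 times = 6 | 0.05/6 = 0.00833 | 2.638 |

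The second threshold is three times stricter. If the bracket were read as dividing by 3 only, the level would be 0.05/3 = 0.0167, which still differs from 0.025.

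**2. Familywise error.** Only two confirmatory tests remain. At 0.00833 each, the Bonferroni bound is 2 × 0.00833 = 0.0167. At 0.025 each it is 0.05, as intended.

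**3. Attempt to reproduce the planned 500.** Under a simple two-mean comparison (1:1, SD 1, difference 0.3, independent observations), total N for 80% power is 4(z_alpha + z_beta)²/0.3², rounded up to whole patients per arm:

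- alpha 0.05: 350
- alpha 0.025: 424
- alpha 0.00833: 540

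None gives 500. The plan used a multilevel simulation whose variance components are not reported, so this does not show that 500 is wrong. It does mean that power figures from the simple model are illustrative.

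**4. Effect of the two rules at 500 analysed, simple model.** The standard error of the difference is sqrt(4/500) = 0.0894.

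- Smallest significant difference: 2.241 × 0.0894 = 0.200 SD, against 2.638 × 0.0894 = 0.236 SD.
- Expected z for a 0.3 difference: 0.3/0.0894 = 3.354.
- Power at 0.025: Φ(3.354 − 2.241) = 86.7% (t test: 86.5%).
- Power at 0.00833: Φ(3.354 − 2.638) = 76.3% (t test: 75.9%).

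**5. Sensitivity to how 500 was reached.** Instead of the simple model, suppose that 500 gives exactly 80% power at a given alpha. The expected z is then z_alpha + 0.842.

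| What 500 delivers | Expected z | Power at 0.025 | Power at 0.00833 |
|---|---|---|---|
| Simple model, independent observations | 3.354 | 86.7% | 76.3% |
| 80% at 0.025 | 2.241 + 0.842 = 3.083 | 80% | about 67% |
| 80% at 0.05, as section {14} states | 1.960 + 0.842 = 2.802 | about 71% | about 56% |

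The six-fold rule costs about 10 to 15 percentage points in every row and falls below 80% in every row.

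**The case against.** The strongest reply is that the intention is easy to recover. The abstract's update note, the outcomes section, the text below Table 2, the sample size section, the trial status section and the opening of section {20a} all point to two primary outcomes. Several of them also place the primary analysis at 6 months. Only the bracket disagrees, and it reads as a remnant of the old design. That is very likely how it arose. But the remnant stands in the operative statement of the confirmatory test, not in a record of changes, and an intention that can be inferred is weaker than a threshold that is prespecified.

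Three further points stand as limits:

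- **Direction.** The six-fold rule is conservative. It creates no excess false-positive risk.
- **Power figures.** The simple model ignores centre clustering and the baseline adjustment, and it does not reproduce the planned 500. If section {14} is taken at its word, with 80% power at an unadjusted 0.05, power per endpoint at 0.025 is also below 80%. The shortfall cannot then be blamed on the six-fold rule alone.
- **SAP.** An analysis plan that is not shown may state the per-test alpha. That would not correct this text, which states the rule twice and differently.

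**Conclusion.** The concern holds. Section {20a} contains two incompatible test counts for one confirmatory analysis, implying 0.025 or 0.0083 per endpoint. The count of six is inconsistent with the rest of the current protocol. A p-value for PI or DS between these values has no defined interpretation.

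This conclusion rests only on the text and on dividing 0.05 by 2 or by 6. The power loss, roughly 10 to 15 points for a 0.3 SD difference with 500 analysed, is secondary and depends on assumptions about the sample size model. The point must be fixed because the threshold is ambiguous, even though the error is on the conservative side.

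**What to change.** In the last paragraph of section {20a}, replace the bracket so that the adjustment covers two outcome measures at one follow-up time, and state the level: PI and DS at 6 months (t2), each tested two-sided at 0.025. Any SAP should carry the same wording.

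In the same edit, correct the visit label. Section {20a} calls the 6-month visit t3, whereas the trial design, outcomes and sample size sections call it t2. Otherwise the corrected sentence would disagree with the model description a few lines above.

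Holm's step-down procedure would keep the familywise level at 0.05 and is never less powerful than Bonferroni. It is optional and not needed to remove the contradiction.

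The cost is one sentence and one label, with no extra patients or data. The change should be made and dated before any outcome results by group are seen.

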### Interim analyses {21b}

N/a. Interim analyses are not planned.

### Methods for additional analyses (e.g. subgroup analyses) {20b}

#### Level of centres

Additional investigations will evaluate existing process and structural parameters as required by the study protocol (e.g. consistency in team collaboration, availability of complete staff, aspects of coordinating treatment groups and plans, qualification of staff, perceived quality of interaction between staff members while conducting group or team meetings).

### Patient level

Parameters for evaluating the delivery of intervention will be gathered during the treatment period (process parameters, see above). Satisfaction of patients with group delivery and perceived relationship and support by caregivers will be evaluated additionally.

Subgroup formation is planned primarily for the centre level. Centres will be grouped according to local parameters (size of community, local health care delivery and networks in terms of pain management), and will consider the process and structural parameters of the centre (main delivery) and delivery of the study intervention.

Subgroup analyses as described above will be conducted as exploratory analyses.

### Methods in analysis to handle protocol non-adherence and any statistical methods to handle missing data {20c}

In longitudinal analyses involving more than one follow-up time point, the family of (generalised) mixed models uses all available data, even if data at some time points are missing. If necessary (e.g. in case of high drop-out-rates > 30%), appropriate methods of (multiple) imputation of missing values will be employed. The population for primary analysis includes all patients for whom PI and DS data are available at baseline and at 6-months-follow-up.

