### Criteria for discontinuing or modifying allocated interventions {11b}

Discontinuation of the study at the participants’ request is possible at any time during participation in treatment or the waiting period without giving reasons.

During participation and waiting period, patients continue to have full access to the health care system (i.e. primary care physicians or specialists). Changes in the participants’ medical treatment are assessed during the individual one-on-one contact with the physician as part of the A-IMPT. In the delayed treatment period of the control group, medical changes will be additionally assessed at the face-to-face interim contact (30 min) 3 months after study inclusion.

Reasons for study discontinuation also include any medical conditions that impact the participant’s ability to continue participating in the A-IMPT, whether they are related to pain or unrelated medical circumstances (e.g. need for urgent surgery or hospitalisation). Exacerbation of pain requiring intensified pain management (inpatient treatment/hospitalisation) will result in study discontinuation. However, discontinuation is not necessary if the pain exacerbation or new-onset pain can be adequately treated (including surgical intervention or short-term opioid prescription, if necessary) without compromising the ability to participate in the intervention (A-IMPT). Furthermore, physiotherapeutic and psychological reasons for study discontinuation are documented during the biweekly team meetings. The decision to discontinue the study is always made collaboratively by the treatment team.

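### The primary analysis is called intention to treat, but its population is patients with observed month-6 data and imputation is left to discretion, so the default confirmatory result is a complete-case estimate

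*Protocol article*

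**What the plan says.** All references are to the protocol article.

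- **Principle.** Section {20a}: "The analysis of the primary endpoints will be conducted according to the intention to treat (ITT) principle".
- **Population.** Section {20c}: "The population for primary analysis includes all patients for whom PI and DS data are available at baseline and at 6-months-follow-up".
- **Model.** Section {20a} takes the 6-month value as the dependent variable in a random-intercept linear mixed model, and "the baseline value at time t_0_ and group membership are used as predictor variables". That section labels the 6-month visit t3, whereas the Outcomes section calls it t2; t2 is used here.
- **Month 3.** The trial-registration note in the abstract: "The primary analysis period is now 6 months without including an additional measurement point after 3 months". The value is still measured: "PI and DS are collected at baseline (*t*_0_) and at 3-, 6-, 9- and 12-month follow-up" (Primary outcomes).
- **Missing data.** Section {20c}: "In longitudinal analyses involving more than one follow-up time point, the family of (generalised) mixed models uses all available data", and then: "If necessary (e.g. in case of high drop-out-rates > 30%), appropriate methods of (multiple) imputation of missing values will be employed".
- **Expected loss.** Section {14} plans for 20% drop-out over 6 months and 782 randomised.
- **Routes out of the study.** Section {11b}: "Exacerbation of pain requiring intensified pain management (inpatient treatment/hospitalisation) will result in study discontinuation". Section {17a} says blinding is not possible.

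**The concern.** The statements in {20a} and {20c} describe different analysis sets. Intention to treat starts from everyone randomised, while {20c} starts from those with observed values at two visits. Someone writing the analysis code cannot follow both.

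The difference affects both confirmatory tests. Patients without month-6 data are removed after randomisation, and the protection that randomisation gives holds only if their absence is unrelated to outcome once baseline and arm are accounted for. There are reasons to doubt that here. Outcomes are patient-reported and unblinded, worsening pain can end participation, and the two arms face different demands (weekly group sessions against a six-month wait). If drop-out depends on interim pain differently in the two arms, the estimated effect moves away from the truth in a direction that cannot be known beforehand.

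**Working it through.** **1. Does the mixed model bring back patients without month-6 data?** No. Section {20c} limits its all-available-data remark to analyses with more than one follow-up time. The primary model has a single follow-up time and uses baseline as a predictor. A patient without the month-6 value contributes no row to the likelihood, and the random intercept does not change that.

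**2. Does imputation bring them back?** Not by rule. It depends on a judgement of necessity, for which 30% is an example. Nothing is fixed for 20%. Imputing month-6 values also sits awkwardly with a population defined by having them.

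**3. How many patients?** Inputs from section {14}: 782 randomised, 20% loss.
- Excluded at 20%: 782 × 0.20 = 156.4, about 156; about 626 remain.
- Excluded at 30%, the example threshold: 782 × 0.30 = 234.6, about 235; about 547 remain.

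Section {14} moves from 500 evaluable to 782 randomised, which implies a loss of 1 − 500/782 = 36.1%, not 20% (500/0.80 = 625). That is a separate sample-size question, and nothing here rests on it.

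**4. Joint PI-and-DS condition.** Read literally, a patient with PI but no DS at month 6 is dropped from the PI analysis too. Both scores come from the same seven-item instrument, so few such patients are likely. The documents give no figure.

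**5. Simple bounds on bias.** Let m be the share missing in an arm and s the amount, in SD, by which its drop-outs are worse than its completers (assumed).

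Bias in favour of the intervention = m(intervention) × s(intervention) − m(control) × s(control).

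- 20% missing in both arms, equal s: 0.20s − 0.20s = 0.
- 20% missing, s = 0.25 to 0.50 in the intervention arm only: 0.20 × 0.25 = 0.05 to 0.20 × 0.50 = 0.10 SD. Against the 0.30 target in section {14}, that is one sixth to one third.

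With no true effect, 625 analysed, SD 1 and two-sided alpha 0.025 (Bonferroni over two endpoints), the standard error is √(4/625) = 0.08. A bias of 0.05 raises the type I error to about 0.055, and a bias of 0.10 raises it to about 0.16.

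**6. Simulation.** Assumptions, none of them from the documents: 391 per arm (782/2), correlations t0–t1 0.50, t0–t2 0.45 and t1–t2 0.65, logit slope of 0.8 per SD of month-3 pain where drop-out depends on it, about 19% missing at month 6, 1,500 trials per scenario. The true effect is set to the planned 0.30 SD.

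| Who leaves | Complete-case ANCOVA | Using t0 and t1 |
|---|---|---|
| Same dependence on month-3 pain in both arms | about 0.30 | about 0.30 |
| Only worse controls | 0.23 | about 0.30 |
| Worse controls and better-off treated patients | 0.18 | about 0.30 |
| Only worse treated patients | 0.36 | about 0.30 |

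A repeat that also assumed a 0.30 SD effect at month 3, with slightly different drop-out intercepts, gave 0.29, 0.24, 0.18 and 0.36 for complete cases and 0.30 in every row when t0 and t1 were used. The last column follows from the set-up, because drop-out was made to depend only on month-3 pain.

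**The case against.** - **Intention to treat can mean analysis by allocated arm regardless of adherence.** Section {20c} reassigns nobody and excludes nobody for non-adherence, so some would call this an available-case or modified version. That is fair as to the label. It does not settle who is in the confirmatory analysis, because the two sections still give different answers.
- **The 30% figure is only an example.** This stands. A reader might infer that imputation is barred below 30%. The text does not say so, and imputation at 20% is permitted. The weakness is that the decision is left open in an unblinded trial.
- **The larger distortions come from chosen scenarios.** This stands too. A reader might infer that any dependence of drop-out on month-3 pain biases the result materially, or that reasons for leaving do differ between arms. The documents support neither. Equal dependence gives almost no bias, and no arm-specific drop-out pattern is reported.
- **Retention measures exist in both arms.** There are individual contacts for the intervention group, a three-month visit for controls, two follow-up actions for late questionnaires, and later access to the programme for controls ({8}, {11c}, {18b}). Section {18b} also plans a list of outcome data for those who discontinue. These steps may reduce the loss, but they do not say how the remaining loss is analysed.
- **Leaving month 3 out is a declared choice, and single-time-point ANCOVA is standard.** True. Using month 3 to inform missing month-6 values does not make it an endpoint and adds no confirmatory test.
- **Imputation details belong in the analysis plan, which is not shown.** Their absence here is not the complaint. The conflict is between two sentences that the article does state.

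**Conclusion.** The point holds as an internal contradiction with a practical consequence. Under the text as written, the default confirmatory estimate is a complete-case one, and about 156 of 782 randomised patients would be left out at the planned 20% loss. Neither the mixed model nor a fixed imputation rule brings them back.

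Bias is possible, not demonstrated. Under the assumed correlations and drop-out patterns, a true 0.30 SD is estimated at anywhere from 0.18 to 0.36, and at about 0.30 when drop-out works alike in both arms. Material bias therefore needs drop-out that differs by arm in its relation to outcome, which the design makes plausible but the documents do not show. The joint PI-and-DS condition is a minor addition. The contradiction itself rests on no assumption and should be resolved before the analysis.

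**What to change.** 1. Reconcile {20a} and {20c}: define the primary population as all randomised patients in their allocated arm, and analyse PI and DS each on its own available data.
2. Prespecify one method that applies whatever the drop-out rate. Either fit a longitudinal mixed model to t0, t1 and t2 with the month-6 contrast as the only confirmatory test, or use multiple imputation by arm with the month-3 value in the imputation model.
3. Keep the completer analysis as a sensitivity analysis.
4. Replace the discretionary wording on imputation with that rule.

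**Cost.** Changed wording in the protocol and analysis plan, and slightly more programming. The data are already being collected, the 6-month endpoint is unchanged and no confirmatory test is added. The method relies on missing at random given t0 and t1, and it does not protect against drop-out that depends on unobserved month-6 pain beyond those values.
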